#### Informational leaflets

Patients presenting with symptoms of a UTI to their GP will receive an information leaflet describing the study, the purpose of the collection of their mobile phone numbers, facts about antimicrobials and the issues surrounding the development of AMR in bacteria. Patients visiting practices from intervention arm B will receive the leaflet with additional information on delayed prescribing of antimicrobials as a potential treatment option for UTIs.

#### Patient education

An infomercial (information commercial) explaining the two key messages (as previously outlined) has been developed for display in practice waiting rooms. An infomercial is a short video representation of information, data or knowledge intended to present complex information quickly and clearly. The infomercial will be displayed in an enclosed and fixed iPad in the practice waiting room. There will also be an option to play an AMR-themed game on this iPad, which will contain the same two messages as stated above. All intervention practices will be offered an iPad for their waiting room at the start of Phase 3 (Figure 
1). The impact of this component on antimicrobial prescribing and consumption will be evaluated in comparison with Phase 2. Both the infomercial and the game will be made freely available for download at the end of Phase 4.

#### The control arm

To gather comparable data on UTI consultations, practices in the control arm will complete a coding workshop at the beginning of Phase 1. For the remainder of the intervention, the control arm will provide 'usual care’ and will receive their audit and feedback reports at the end of intervention Phase 3. Practices in the control arm will also submit urine samples from UTI patients and request patients’ mobile telephone numbers for the duration of the intervention.

#### Ethical approval

Ethical approval including a patient opt-out methodology was obtained from the Irish College of General Practitioners.

#### Informed consent

Informed consent for practice participation in the intervention and for the remote extraction of anonymized UTI patient consultation data through the iPCRN will be obtained from the practices at the start of the coding workshop in Phase 1. Each practice will also receive posters to display in their waiting room to inform patients of the practice’s decision to participate in the SIMPle study. The GP will request the patient’s mobile telephone number and outline the aim of the study during the UTI consultation. Patients will be required to confirm their consent by replying to the first text message they receive before continuing with the text-messaging process.

### Quantitative data collection

Data collection will involve five quantitative components: consultation data obtained through the iPCRN; questionnaire data from the GPs, along with a practice profile from the practice manager; Health Service Executive Primary Care Reimbursement Services (HSE-PCRS) prescribing data; and patient follow-up information through text messages. Data for the GPs will be collected at the beginning of Phase 1, immediately after the patient education intervention (Phase 3) and after a six-month follow-up (Phase 4). The collection of patient data will continue throughout Phases 2 and 3.

#### Consultation data

For the purpose of the intervention, UTI consultation data will be extracted remotely through the iPCRN. Extracted anonymized consultation information will be comprehensive and will include, at a practice level:

• Total number of consultations per month;

• Total number of consultations for UTIs per month (coded U71);

• Practice information (GPs, practice nurse, dispensary);

• Number of times an audit was generated (to monitor coding).

For the patients, the following information will be collected:

• Consultations (numbers, dates);

• UTI consultations (dates);

• Urine sample results (date, outcome, resistance profile);

• Antimicrobial prescribing (type, date, dosage);

• Other prescribed medication (type, date, dosage);

• Demographic data including age, sex, medical card status and comorbidities (if coded).

#### Questionnaires

Additional information collection will take place at primary points throughout the intervention, including the administration of a questionnaire to collect data on knowledge and attitudes towards antimicrobial prescribing by GPs. This questionnaire will be administered to GPs at the beginning of Phase 1, at the coding workshop and at the end of Phase 3, to measure potential changes in knowledge, attitudes and behaviours of GPs in each arm. A practice profile will be completed at the beginning of Phase 1, to determine number of whole-time equivalent GPs and practice size.

#### Health Service Executive Primary Care Reimbursement Services

The HSE-PCRS provides free health services under the General Medical Services scheme. Approximately 30% of the Irish population is entitled to free medical care, including medication under this scheme. Regional prescribing data from practices in the study will be compared with HSE-PCRS data
[70].

#### Follow-up data

Evaluative information from the patients will be obtained via text message. These text messages will require a minimal response (at no cost) from the patient and will be used to assess actual consumption of the prescribed antimicrobial. Patients can discontinue receiving these text messages at any time by replying STOP.

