#### Secondary outcome: decrease in the quantity of consumption (control - intervention arm B)

To estimate the potential power to detect this secondary outcome, an additional sample size calculation was carried out.

• 56% of the patients presenting with a UTI, and for whom a urine sample was submitted for microbiological analysis, received a prescription
[8].

• A 20% decrease in consumption can be achieved through delayed prescribing
[42].

Taking account of the cluster effect and based on previous ICC estimates, a total sample size of 240 patients recruited from 20 practices gives a power of 80% to detect a significant change in the proportion of patients who reduce antimicrobial consumption through delayed prescribing if the ICC is 1%.

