#### Outcome: frequency of antimicrobial prescribing and consumption

The frequency of antimicrobial prescribing will be compared between the control and each intervention arm (arms A and B).

• Consultations will be analyzed according to whether an antimicrobial was prescribed or not (yes/no).

• The prescription rates per group per month for each antimicrobial group will be calculated as the number of antimicrobial prescriptions per 1,000 consultations per month.

• Comparison of the overall reduction over the period of the intervention will be based on the percentage of consultations where an antimicrobial was prescribed at the start of the intervention, as compared with the end.

The frequency of antimicrobial consumption will be compared between intervention arms A and B, according to their response to the text messages.

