### Method of quantitative data analysis

Quantitative analysis will be undertaken using SPSS for Windows release 20.0 (SPSS Inc., Chicago, IL, USA) and Stata 11 (Stata Corporation, Texas). Multilevel analysis will be performed using MLwiN version 2.21 software and cost-effectiveness analysis will be conducted using Excel and Stata 11. Statistical significance will be set at the 5% level for all outcomes.

Multivariate analysis will examine intervention and control arm changes from baseline measures and will follow the principle of intention to treat. Outcomes will be compared between intervention (arms A and B) and the control arm, using a multilevel logistic modelling approach to control for baseline prescribing as well as other confounding variables at patient and practice level. All statistical analysis will be undertaken in accordance with current guidelines for randomized controlled trials
[71].

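### Antimicrobial consumption is sized as a proportion of all UTI patients, but the text messages are described as measuring use of the prescribed drug, with no stated denominator or rule for patients given no prescription

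*Protocol article*

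**What the plan says.** All references are to the protocol article.

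- **Objective.** The first item under Secondary objectives concerns prescribing and consumption in patients who consult with a UTI. It is not limited to those given a prescription.
- **Sizing.** The sample size section for the secondary outcome (control v arm B) takes as its starting point that "56% of the patients presenting with a UTI, and for whom a urine sample was submitted for microbiological analysis, received a prescription", adds that "A 20% decrease in consumption can be achieved through delayed prescribing", and concludes that "a total sample size of 240 patients recruited from 20 practices gives a power of 80"%. It words the target as power "to detect a significant change in the proportion of patients who reduce antimicrobial consumption through delayed prescribing".
- **Who is texted.** Under Patient enrolment, GPs are to request a mobile number from each patient with a suspected UTI. No prescription is required.
- **What the texts measure.** Under Follow-up data, the messages "will be used to assess actual consumption of the prescribed antimicrobial".
- **Analysis.** Under the outcome on frequency of prescribing and consumption, consumption is compared between arms "according to their response to the text messages", with no denominator. The same section separately classifies every consultation by whether an antimicrobial was prescribed, and compares control with each arm.
- **Delayed prescriptions.** The outcome on delayed prescribing counts them as a share of overall UTI prescribing.

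**The concern.** One outcome rests on two populations. The objective and the sizing use all UTI patients. The description of the measurement uses patients who hold a prescription. On the plan's own 56%, the remaining 44% fall between the two: they are in the text follow-up, but the article does not say how they count.

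This matters because arm B can lower consumption in two ways. The shared discussion may end without a prescription, or a delayed prescription may be issued and never taken. A comparison among prescribed patients sees only the second. It also compares groups selected by a decision that follows randomisation and that the intervention is meant to influence, so the protection of randomisation is lost. Depending on which section the analyst follows, the same trial could show a large effect on consumption or none.

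**Working it through.** **1. Reproduce the 240.** Inputs: p1 = 0.56 and a 20% decrease read as 20 points, so p2 = 0.36; power 80%; ICC 0.01; 20 practices (all from the secondary sample size section); alpha 5% (Method of quantitative data analysis). Assumed, because not stated: two-sided test, 10 practices per arm, continuity correction.

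- Uncorrected n per arm = [1.96·√(2·0.46·0.54) + 0.8416·√(0.56·0.44 + 0.36·0.64)]² / 0.20² = 96.3, so 97.
- With continuity correction: 107 per arm.
- Patients per practice, m = n(1 − ICC)/(k − n·ICC) = 107·0.99/(10 − 1.07) = 11.86, rounded up to 12.
- Total = 12 × 20 = **240**, as stated.

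Other readings do not give 240. Without the correction the total is 220. A relative 20% decrease (56% to 44.8%) needs 900, or 980 with the correction. A prescribed-only fall from 100% to 80% needs 80, or 100 with the correction. With the stated 56% as input, the sizing is therefore on all UTI patients. It uses a prescribing rate as the control consumption rate, which counts unprescribed patients as non-consumers and takes every control prescription as used.

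**2. Translate the sized effect to prescribed patients.** Let f be the share of the 20-point fall that comes from not prescribing. Arm B then prescribes to 0.56 − 0.20f, and the proportion taking the drug among those prescribed is 0.36/(0.56 − 0.20f). In control it is 0.56/0.56 = 100%.

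| | Prescribed, of all | Took it, of all | Took it, of prescribed |
|---|---|---|---|
| Control | 56% | 56% | 100% |
| Arm B, f = 0 (all untaken) | 56% | 36% | 0.36/0.56 = 64% |
| Arm B, f = 0.5 | 46% | 36% | 0.36/0.46 = 78% |
| Arm B, f = 1 (all not prescribed) | 36% | 36% | 0.36/0.36 = 100% |

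**3. Read the columns as outcomes.** From f = 0 to f = 1:

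- The prescribing outcome shows a difference of 0, 10 and 20 points.
- Prescribed-only consumption shows 36, 22 and 0 points.
- Consumption among all patients shows 20 points each time.

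Only the last is the quantity sized, and only it captures both routes.

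**4. Check whether a prescribed-only analysis would be underpowered.** With 56% prescribed in both arms, 240 patients yield 240 × 0.56 ≈ 134 (67 per arm, 6.7 per practice, design effect 1 + 5.7 × 0.01 = 1.057). Power for a 20-point fall, without continuity correction, is about 97% from 100%, 89% from 95%, 81% from 90% and 70% from 80%. The control levels are assumptions.

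**The case against.** The strongest reply is that this is silence in a condensed article, not a rule that drops patients. The follow-up section states the purpose of the texts in one clause and defines no analysis population. All suspected-UTI patients enter texting, and nothing prevents unprescribed patients from being counted as non-consumers. Coding of a secondary outcome is often left to a fuller document. The sizing also attributes the reduction to delayed prescribing, for which use among prescribed patients is a relevant measure.

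Much of this stands, and it rules out several stronger readings that a reader might infer:

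- *That a fall through less prescribing would be invisible.* It would not: prescribing is compared for every consultation as its own outcome.
- *That the 44% have no score, or that texting is the only source.* The article neither scores nor excludes them. The online survey also asks about consumption, though only of patients already followed up.
- *That 240/0.56 ≈ 429 patients are needed.* This assumes that 240 prescribed patients are required. Step 4 shows no general shortfall; power drops below 80% only at lower assumed control use.
- *That a within-patient change is planned.* The phrase about patients who reduce consumption is loose wording; the 240 is an ordinary two-proportion comparison.
- *That a null result is likely.* The 100% v 100% case needs the whole fall to come from not prescribing and every issued prescription to be taken. It is a limiting case.

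What the reply does not remove is the conflict in the text itself: a sizing and an objective on all UTI patients, and a measurement worded for prescribed patients. Nor does the prescribing outcome close the gap, because an untaken delayed prescription apparently still counts as prescribed.

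**Conclusion.** The point holds as a mismatch between the quantity sized and the quantity described as collected. Under the sized effect, the prescribed-only contrast can lie anywhere from 100% v 64% to 100% v 100%, while the all-patient contrast stays at 56% v 36%. No stated outcome clearly combines patients not prescribed with prescriptions not taken, although the article's limitations section gives evaluation of consumption, beyond GP prescribing, as the reason for using texts.

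The figures assume an absolute 20-point decrease, a two-sided 5% test, 10 practices per arm and full use of control prescriptions. The split between the two routes is illustrative. The issue concerns a secondary outcome, but the one tied to arm B's distinctive component. It should be corrected; it does not touch the primary outcome.

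**What to change.** - Define the outcome as: took any antimicrobial for this UTI episode (yes/no), among all UTI patients who consent to texting. Score no prescription, or a prescription not taken, as not consumed.
- Reword Follow-up data to match, with a text question that a patient without a prescription can also answer.
- In the secondary sample size section, replace the phrase about patients who reduce consumption with this proportion, and state the same denominator in the consumption analysis.
- Report use among prescribed patients as a descriptive breakdown only.

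The 240 is unchanged, because this is the quantity it was calculated for. It also survives some non-use in control: 50% v 30% again gives 240 by the method of step 1 (103 per arm, 11.37 rounded up to 12 per practice). The cost is outcome wording and one text question. Unprescribed patients are already due to be texted, so no further patients or procedures are needed.

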#### Online survey

After clearance of symptoms, assessed via text messaging, patients who were followed up will be invited to complete a brief online survey. This survey includes questions regarding the patient’s attitudes to antimicrobials, consumption of antimicrobials and awareness of the potential implications of AMR. Patients will be incentivized to complete the online survey.

### Quantitative data analysis

Data comparisons will be made between the start and end of the intervention. To assess sustainability, an additional comparison will be made six months after the end of the intervention. An overview of the data collected through the iPCRN, as outlined in data collection, will be presented for both practice and patient variables. Data will be presented and compared between each arm. Patients’ characteristics will be compared between the group who were followed up by text messaging and the group who did not participate in text messaging.

#### Primary outcome: adherence to the guidelines for antimicrobial prescribing in primary care in Ireland

Comparison of antimicrobial prescription data will be made between control and intervention arm A.

• Each consultation will be categorized according to whether an antimicrobial was prescribed (yes/no) and if so, whether first-line antimicrobials were prescribed (yes/no).

• Antimicrobial prescribing rates will be determined for each intervention arm per month for first-line, second-line and other antimicrobials as specified in the Guidelines for Antimicrobial Prescribing in Primary Care in Ireland.

• The proportion of antimicrobial prescribing according to first-line treatment for each intervention arm will be calculated by determining the number of first-line prescriptions as a percentage of the total number of antimicrobial prescriptions for UTIs.

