#### Secondary objectives

1. To compare the effect of the intervention on the frequency of antimicrobial prescribing and antimicrobial consumption in patients presenting with a UTI.

2. To measure the uptake and impact of delayed antimicrobial prescribing for UTIs and the impact of this treatment approach on UTI GP reconsultation visits.

3. To assess a change in cognitive beliefs (knowledge and attitudes) of GPs related to antimicrobial prescribing.

4. To conduct a cost-effectiveness and process evaluation of the SIMPle intervention.

5. To compare the prescribing rates of the intervention arms with regional UTI antimicrobial prescribing rates.

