### Sample size

#### Primary outcome: adherence to the guidelines for antimicrobial prescribing in primary care in Ireland (control - intervention arm a)

Previous research has established that 56% of UTI patients receive an antimicrobial, with only 38% of prescriptions made out for the recommended first-line treatment
[8]. Sample size calculations are based on an absolute 10% increase in first-line prescriptions according to guidelines (primary outcome).

Additional assumptions for sample size calculations are:

• Power of 80% and *α* of 5%.

• Practice attrition is dependent on the completeness of consultation coding, which will be monitored and corrected during Phase 1.

• Patient attrition will be close to 0%, as all coded consultations will be included.

• Improvement in the control group due to participation in the coding workshops has been anticipated.

• An intracluster correlation (ICC) of 1% was obtained from a previous study in this area
[6,12].

A total sample size of 920 patients recruited from 20 practices gives a power of 80% to detect a significant change in the proportion of patients to receive first-line antimicrobial when treated for UTI when the ICC is 1%.

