### GP components

#### Intervention workshops

A coding workshop will be delivered to all practices at the beginning of Phase 1. Routine coding for UTIs using the International Classification of Primary Care code (U71: 'cystitis, urinary infection, other’) will be demonstrated. The advantage of routine coding of UTI consultations will be to facilitate the generation of electronic audit and feedback reports, which will be extracted through the iPCRN system (see further).

Contact information for GPs (for example, mobile telephone numbers, email addresses) will also be collected to facilitate reminders to code throughout the study period.

Phase 2 will begin with an interactive workshop for intervention arms A and B. The interactive workshops promote changes (where necessary) in antimicrobial prescribing for the treatment of UTIs by presenting an overview of prescribing and AMR, discussing the role of the GP in the spread of AMR and the potential positive impact of prescribing according to guidelines.

In addition, the interactive workshop delivered to practices in intervention arm B will support the GPs in recommending delaying antimicrobial treatment by 48 hours where appropriate. Based on the information provided in the workshop, the GP can discuss the benefits of delayed antimicrobial treatment for UTIs with the patient. This two-way communication will encourage patients to make an informed decision on their treatment. The decision to delay treatment will be shared between the GP and the patient.

The workshops will be delivered to each practice by members of the research team. General practitioners attending the workshops can receive continued professional development recognition for their participation from the Irish College of General Practitioners.

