#### Outcome: reconsultation visits

Reconsultation will be determined by the number of reconsultation UTI visits to the GP within one month of initial treatment.

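### The reconsultation window starts at initial treatment, a date that untreated patients do not have; count it from the index consultation, and add an index-only sensitivity analysis of the primary outcome

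*Protocol article*

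**What the plan says.** **Reconsultation.** The Protocol article defines the outcome in one sentence, under *Outcome: reconsultation visits*: "Reconsultation will be determined by the number of reconsultation UTI visits to the GP within one month of initial treatment". Its purpose is the second of the *Secondary objectives*: "To measure the uptake and impact of delayed antimicrobial prescribing for UTIs and the impact of this treatment approach on UTI GP reconsultation visits". Under *Intervention workshops*, the arm B workshop "will support the GPs in recommending delaying antimicrobial treatment by 48 hours where appropriate". *Sample size* states that 56% of UTI patients receive an antimicrobial.

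*Consultation data* lists what is extracted for each patient, including dates of consultations, UTI consultations and antimicrobial prescriptions. It lists no date of first intake. Actual consumption comes from text messages (*Follow-up data*).

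**Primary outcome.** In the analysis section, "Each consultation will be categorized according to whether an antimicrobial was prescribed (yes/no) and if so, whether first-line antimicrobials were prescribed (yes/no", and the result for each arm is "the number of first-line prescriptions as a percentage of the total number of antimicrobial prescriptions for UTIs". *Sample size* adds: "Patient attrition will be close to 0%, as all coded consultations will be included". Its total, 920 from 20 practices, is expressed in patients. The article has no rule limiting the primary outcome to the first consultation of an episode.

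**The concern.** The reconsultation outcome has to answer whether delaying, or not giving, an antimicrobial brings patients back. A window opened by treatment does not suit that question. Patients who get no antimicrobial fall outside the definition, and a delayed prescription has more than one possible start. Treatment also happens after randomization, and the trial sets out to change it: the first secondary objective compares the frequency of prescribing and consumption between arms. If the arms differ in who is treated, a comparison among treated patients sets different mixes of patients against each other, and randomization no longer protects it.

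The primary outcome raises a related but weaker question. A return visit coded U71 that ends in a second prescription counts as one more prescribing decision. The drug chosen then may differ from the first choice, and the number of such visits may depend on the arm.

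**Working it through.** **Step 1. Who has a time origin?** Three readings of the reconsultation definition, set against the kinds of patient in the trial:

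| Reading of the origin | No prescription | Delayed, never taken | Delayed, taken after 48 hours |
|---|---|---|---|
| First intake | none | none | about 2 days after the consultation |
| Prescription | none | prescription date | prescription date |
| Initial consultation | consultation date | consultation date | consultation date |

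Only the third reading covers every coded patient, and the sentence does not state it. The first reading cannot be built from the extracted record, because intake is known only for patients who take part in text messaging.

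**Step 2. How many have no origin under either treatment-based reading?** The inputs are in *Sample size* and *Feasibility*. The plan's own figures reproduce:

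- Samples in six months from 20 practices: 364 × 0.5 × 20 = 3,640.
- Prescribed an antimicrobial: 3,640 × 0.56 = 2,038.4, printed as 2,038.
- Not prescribed: 3,640 − 2,038 = 1,602, and 1,602 / 3,640 = 44%.

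The protocol treats samples as patients here, and the 56% comes from earlier research. The 44% is therefore a planning figure, not a forecast for any one arm.

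**Step 3. How can return visits move the primary percentage?** Let *s* be the share of an arm's UTI prescriptions written at return visits, *p* the first-line share at index visits and *q* the first-line share at return visits. The arm's percentage is (1 − *s*)·*p* + *s*·*q*. The documents give neither *s* nor *q*. For illustration only, assume that 38% and 48% are index-visit shares and that *q* is the same in both arms, anywhere from 0 to 38%.

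| *s* control | *s* arm A | Difference at *q* = 0 | Difference at *q* = 38% |
|---|---|---|---|
| 10% | 10% | 43.2 − 34.2 = 9.0 | 47.0 − 38.0 = 9.0 |
| 10% | 20% | 38.4 − 34.2 = 4.2 | 46.0 − 38.0 = 8.0 |
| 10% | 5% | 45.6 − 34.2 = 11.4 | 47.5 − 38.0 = 9.5 |

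Differences are in percentage points. The table shows only that unequal return visits could push the result either way while index prescribing stays the same. It does not estimate what will happen.

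**Step 4. Would an index-only analysis have enough data?** Take the projected 2,038 prescriptions (1,019 per arm, 10 practices per arm), ICC 0.01 and 38% v 48%. Assume a two-sided 5% test, since sidedness is not stated. If a fraction *r* of patients has one repeat treated visit, index patients per arm are 1,019 / (1 + *r*). The design effect is 1 + (*m* − 1) × 0.01, with *m* the number per practice. Power from the normal approximation for two proportions:

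- all 1,019 per arm (*m* = 101.9, design effect 2.01): 89.7%
- *r* = 5%, 970 per arm: 89.0%
- *r* = 30%, 784 per arm (design effect 1.77): 85.3%

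At the projected volume, an index-only sensitivity analysis is informative across this assumed range.

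**The case against.** **On the primary outcome, the case for the plan is strong.** The trial targets GP prescribing. The primary objective, the 38% and the planned 10-point increase are all framed as prescriptions, and the computer prompt appears whenever U71 is entered, so a return visit is also an exposed decision. Counting every coded consultation is a coherent target. A reader might infer from Step 3 that the planned difference is diluted and the trial loses power. The documents do not support that: nothing says that the 38% or the 10 points exclude return visits, and if they already include them there is nothing to dilute. Delay is also promoted only in arm B, whereas the primary contrast is control against arm A. What stands is narrower: repeat prescriptions arise after randomization and may differ by arm. The multilevel model adjusts for patient-level variables, but even a patient-level random effect would deal with correlation, not with the mix of first and repeat prescriptions.

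**On reconsultation,** the authors may have meant the initial consultation, and a 48-hour shift is small in a one-month window. A reader might also infer from the 20% fall in consumption assumed for arm B that a matching share of its patients drops out of this outcome. That does not follow. A patient with a delayed prescription who never takes it still has consultation and prescription dates, and the protocol does not say whether the 20% is absolute or relative. The objection does not reach patients given no prescription, who have no origin under either treatment-based reading.

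**On what an article may omit,** episode rules can be left to an analysis plan. Here, however, the article does fix a time origin, and that origin fits the objective badly.

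**Conclusion.** The reconsultation definition should be changed. Followed as written, it leaves about 44% of UTI patients without a start date, on the protocol's 56%. It is ambiguous for delayed prescriptions, and it conditions the arm comparison on an event that the intervention is intended to alter. The size and direction of any resulting error cannot be given, because the protocol states no reconsultation rates. The outcome is secondary, but it is the one meant to show the consequence of delaying for return visits.

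For the primary outcome, the all-consultation analysis is defensible and no error is shown. The possible influence of return visits is of unknown size and warrants a sensitivity analysis, not a new primary definition. That return visits enter at all is inferred from the inclusion of every coded consultation and the absence of an index rule. It applies only to visits coded U71 at which a prescription is issued.

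**What to change.** 1. Under *Outcome: reconsultation visits*, define an index consultation as the first U71 consultation of an episode, for example one with no U71 consultation in the previous month. Count U71 visits in the month after it for every coded patient, whether treated, delayed or untreated, and compare arms on that full denominator.
2. For the primary outcome, keep the analysis of all coded consultations and add a sensitivity analysis restricted to prescriptions at index consultations. Report the number of return-visit prescriptions by arm beside it.

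The cost is a data step. The consultation and prescription dates are already in the extraction, and the two-month Phase 1 coding period supplies the look-back for early Phase 2 visits. Episodes that open in the last month of Phase 3 need one more month of extraction to complete their window. Sample size, recruitment and patient care do not change.
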